## **b. Definitions**

### **Contact**

According to the WHO and the European Centre for Disease Prevention and Control (ECDC) a contact of a COVID-19 case is any person who has had contact with a COVID-19 case (Annex 2) within a timeframe ranging from 48 hours before the onset of symptoms of the case to 14 days after the onset of symptoms (22).

If the case had no symptoms, a contact person is defined as someone who has had contact with the case within a timeframe ranging from 48 hours before the sample which led to confirmation was taken, to 14 days after the sample was taken. The associated risk of infection depends on the level of exposure.

Since local and community transmission has been reported in Spain and in the study areas, all patients presenting with symptoms of acute respiratory infection in primary care or the emergency department of a hospital (first contact with the healthcare system) will be considered as suspected cases.

### **Probable case**

A suspected case for whom testing for virus causing COVID-19 is inconclusive (according to the test results reported by the laboratory) or for whom testing was positive on a pan-coronavirus assay.

### **Confirmed case**

A person with laboratory confirmation of virus causing COVID-19 infection, irrespective of clinical signs and symptoms.

### **Clinical severity**

The definitions for mild and severe illness are in Annex 3, while those with critical illness are defined as patients with acute respiratory distress syndrome or sepsis with acute organ dysfunction. Mild illness will be considered in case of patients with uncomplicated upper respiratory tract viral infection, or non-specific symptoms such as fever, fatigue, cough (with or without sputum production), malaise, muscle pain, sore throat or dyspnea. Patients may also present with diarrhoea, headache, anosmia or taste disorders or non severe pneumonia (suspected respiratory infection without severity criteria -respiratory rate > 30 breaths/min; severe respiratory distress; or SpO2 ≤ 93% on room air).

### **Prolonged QTc interval**

The QT interval is dependent on the heart rate and should be adjusted to improve the detection of patients at increased risk of ventricular arrhythmia. The most commonly used QT correction formula is the Bazett's formula, calculating the heart rate-corrected QT interval (QTcB). Bazett's formula is often given in a form that returns QTc in dimensionally suspect units, square root of

seconds. The mathematically correct form of Bazett's formula is:  $QTcB = QT / \sqrt{RR}$ . A QTc above 500 ms and/or QTc  $\geq 25\%$  from baseline. will be considered abnormal (23).

### **c. Study procedures**

#### **Enrolment**

Participants will be enrolled in the study following the steps described below.

##### **a) Screening**

At each hospital several recruitment approaches will be used, including:

- Prenatal antenatal care and routine prenatal ultrasonography
- The emergency room at the study hospitals
- Referrals from other providers SARS-CoV-2 testing sites and laboratories
- Use of online and social networking websites and apps

Pregnant women who undergo routine follow up at the recruitment hospitals (prenatal visits or obstetric screening ultrasounds) will be provided an informative study leaflet and be invited for study eligibility assessment while they are waiting to be attended. Study personnel will explain the study details to the women who accept to participate in the screening procedures.

##### **b) Informed Consent**

Those women who fulfil the inclusion criteria and accept to participate will be asked to sign an informed consent form. This will be obtained before any study procedures and tests are initiated. The informed consent will cover the woman and the newborn (Annex 4).

##### **c) Electrocardiogram**

An electrocardiogram (ECG) will be performed using a mobile device (Kardia®). If the QTc is > than 500 milliseconds the woman will be considered as “study screening failure” and she will not be included in the study. If the QTc is < than 500 ms the recruitment procedures will continue.

##### **d) Demographic, obstetric and medical data**

The woman's demographic and medical and obstetric data will be recorded onto a specific electronic case report form (eCRF). The physical examination of the woman at the ANC visit will be recorded and will include the following assessments: weight, height, gestational age by first trimester ultrasound assessment.

##### **e) SARS-CoV-2 testing**

A nasopharyngeal and oropharyngeal swabs of all included women will be collected for SARS-CoV-2 diagnosis by PCR. Additionally, 5 ml of venous blood will be collected for SARS-CoV-2 serologic analysis of all participants at baseline.

### **Randomization**

#### **a) Study groups**

Based on the presence of signs and symptoms and SARS-CoV-2 PCR results, participants will be assigned to one of the following study groups:

- Symptomatic women (mild disease)
  - PCR-confirmed SARS-CoV-2 infected → will be considered symptomatic infected

- PCR-negative SARS-CoV-2 -> will be considered not infected and will be withdrawn from the study unless reporting having been in contact with a COVID-19 confirmed or suspected case in the previous 14 days
- Asymptomatic women who are contacts with a confirmed or suspected case
  - PCR-confirmed SARS-CoV-2 infected → will be considered asymptomatic infected
  - PCR-negative SARS-CoV-2 infected → will be considered contact uninfected

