#### **Household and follow-up visits**

At day 21 after initiating study drugs' administration (one week after treatment completion), study personnel will visit women at home or at the hospital to collect a nasopharyngeal and oropharyngeal swabs for PCR -SARS-CoV-2 and to perform an ECG.

The study personnel will assess treatment adherence by requesting and counting if there are remaining study pills.

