| Demographics/medical history                                                                                                                                                      | x                           |                                            |                                                               | x                      |                                      |                             |
| Physical/clinical examination                                                                                                                                                     | x                           |                                            |                                                               | x                      |                                      |                             |
| Concomitant medication                                                                                                                                                            | x                           |                                            | x                                                             | x                      | x                                    |                             |
| Gestational age                                                                                                                                                                   | x                           |                                            | x                                                             | x                      | x                                    |                             |
| 
 
Nasopharyngeal and oropharyngeal swabs for maternal SARS-CoV-2 PCR
 
Venous blood (5 ml, IgG and IgM against SARS-CoV-2)
 
 | x                           |                                            | x                                                             |                        |                                      |                             |
| Maternal and perinatal outcome                                                                                                                                                    |                             |                                            |                                                               |                        | x                                    |                             |

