#### **Statistical models and methods of analysis**

The primary analysis of the trial will be:

- The comparison of the proportion of negative SARS-CoV-2 PCR at day 14 after initiating treatment administration among those women who were SARS-CoV-2 PCR positive at recruitment in the ITT and ATP cohorts.
- The comparison of the proportion of pregnant women who were negative SARS-CoV-2 PCR at recruitment and close contacts of confirmed cases of SARS-CoV-2 infection, with a positive PCR for the infection at day 14, in the ITT and ATP cohorts.

Proportions will be compared between the two intervention-arms within each group using the Fisher exact test and presented as relative risk ratio (RR) or reduction of the RR ( $1 - RR * 100\%$ ) if RR lower than 1. Adjustment for co-variables and possible confounders will be done using Poisson regression with a log link and robust estimate of the covariance (Huber method), using the method proposed by Zou et al. 2014 and 2013.

Continuous variables will be compared between groups using Wilcoxon rank sum test and the effect presented as Mean Difference. Adjustment for co-variables and possible cofounders will be done using ordinary least square regression. Variables will be transformed to the logarithm scale if normality is improved and results presented as Proportional Difference. If after transformation, non-normality of the residuals is detected using diagnostic regression plots, robust intervals of confidence and Wald test will be presented instead.

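### Uninfected contacts and incident infection are defined by PCR alone, so women infected before entry can dilute the prevention comparison although baseline serum is collected from everyone

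*Protocol*

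**What the plan says.** Primary objective 2 (section 4) concerns incident infection in contacts, and Sample size (section 5.a) sizes the comparison for contacts who are not infected.

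- **Group assignment** (5.c, Randomization, a) Study groups) does not use serology: "Based on the presence of signs and symptoms and SARS-CoV-2 PCR results, participants will be assigned to one of the following study groups". An asymptomatic contact with a negative PCR "will be considered contact uninfected". A symptomatic PCR-negative woman "will be considered not infected and will be withdrawn from the study unless reporting having been in contact" in the previous 14 days.
- **Baseline tests** (5.c, e) SARS-CoV-2 testing): "A nasopharyngeal and oropharyngeal swabs of all included women will be collected for SARS-CoV-2 diagnosis by PCR", with no repeat or confirmatory swab stated. Then: "Additionally, 5 ml of venous blood will be collected for SARS-CoV-2 serologic analysis of all participants at baseline".
- **Prevention analysis** (5.i, Statistical models and methods of analysis): the denominator is "pregnant women who were negative SARS-CoV-2 PCR at recruitment" who are contacts, and the event is a positive PCR. Neither a confirmatory swab nor seroconversion is required. Arms are compared with the Fisher exact test.
- **Populations** (5.i): the intention-to-treat efficacy set is all randomised women. No population, inclusion criterion or exclusion criterion mentions serostatus or earlier infection.
- **Day-21 blood**: Table 1 lists "Venous blood (5 ml, IgG and IgM against SARS-CoV-2") in the same row as the maternal swabs, and that row is marked at enrolment and at the visit 7 days after treatment. The text on that visit sends staff only "to collect a nasopharyngeal and oropharyngeal swabs for PCR -SARS-CoV-2 and to perform an ECG".

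**The concern.** A negative swab on one day shows that viral RNA was not detected that day. It does not show that the woman has not been infected. Contacts qualify on exposure in the past 14 days, and the sites lie in the two regions that the protocol describes as the more severely affected in Spain. Some contacts could therefore have been infected before entry and be PCR-negative when sampled. Preventing new infection is not possible in such women, yet a positive follow-up swab in one of them counts as an event.

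The comparison has little room for such events. It is sized on 3% against 0%, which is about 8 control events (0.03 × 257 = 7.7) and none on hydroxychloroquine. The sample that could identify many of these women is already collected, before randomisation, and the stated definitions leave it unused.

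**Working it through.** **1. The plan's own figure.** Inputs from Sample size: 3% in controls, a reduction of 3 percentage points (so 0% on hydroxychloroquine), 80% power, two-sided 0.05, 1:1. With pooled variance under the null, p̄ = 0.015:

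n = [1.960·√(2·0.015·0.985) + 0.8416·√(0.03·0.97)]² / 0.03² = (0.3369 + 0.1436)² / 0.0009 = 256.5, so 257 per arm. The stated figure reproduces. Exact power of the planned Fisher test at 257 per arm is 78%.

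**2. How few stray events matter.** Control events needed for Fisher p ≤ 0.05 at 257 per arm:

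| Events on hydroxychloroquine | Control events needed |
|---|---|
| 0 | 6 |
| 1 | 8 |
| 2 | 10 |

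One event on hydroxychloroquine already requires slightly more than the expected control count of 7.7. This step assumes nothing about serology.

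**3. Carry-over model.** Two quantities are assumptions, because the documents give no value for either:

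- s = share of PCR-negative contacts already infected, and seropositive, at entry;
- q = chance that such a woman swabs positive at the endpoint, taken as equal in both arms.

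Control rate = (1 − s)·3% + s·q. Hydroxychloroquine rate = s·q. Example with s = 10%, q = 5%: control 2.7% + 0.5% = 3.2%; hydroxychloroquine 0.5%; RR = 0.5/3.2 = 0.16; carry-over 257 × 0.005 = 1.3 women per arm.

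Exact Fisher power, all PCR-negative contacts, 257 per arm (expected RR in brackets):

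| q | s = 5% | s = 10% | s = 15% |
|---|---|---|---|
| 0 | 74% (0) | 69% (0) | 64% (0) |
| 1% | 72% (0.02) | 65% (0.04) | 58% (0.06) |
| 5% | 64% (0.08) | 52% (0.16) | 42% (0.23) |
| 10% | 56% (0.15) | 42% (0.27) | 32% (0.37) |

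**4. Restricted to baseline-seronegative women.** About 257·(1− s) per arm, that is 244, 231 or 218, at 3% against 0%: power 74%, 69% or 64%, and RR 0, for every q. At q = 0 the restriction gains nothing and costs at most about 0.2 percentage points. For q above 0 it gains from about 2 points (s = 5%, q = 1%) to 32 points (s = 15%, q = 10%).

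**5. Numbers needed.** To keep 257 seronegative women per arm: 257/0.95 = 271, 257/0.90 = 286, 257/0.85 = 303.

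**The case against.** **This belongs in the analysis plan.** Section 5.i says that a data analysis plan will be developed, and a serostatus subset is a common item there. The PCR-based rule is also coherent and matches the third hypothesis, which speaks of PCR-negative contacts. What stands: a seronegative supporting analysis could well appear in an unseen plan. But the protocol itself fixes the primary population and event on PCR, while its objective and sample size are about incident infection in uninfected women. That is a stated choice, not a gap.

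**The size is assumed.** A reader might infer that a later positive swab in a seropositive woman is residual shedding, or that power will fall to 32–56%. The documents support neither. They give no seroprevalence, antibody timing or rate of repeat positivity. Such a positive could be a new infection, and the antibody result could be false. At q = 0 restriction gains nothing. This objection stands in full, so only a range can be given.

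**The fragility comes from sizing on 0%.** True. With no seropositive women at all, 0.5% breakthrough on hydroxychloroquine cuts Fisher power from 78% to 46%. Carry-over is one avoidable source of such events, not the only one.

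**The remedy has limits.** The serological assays section says the immunoassay is still being developed and names alternatives; no cut-off is given. False positives would remove uninfected women, and the restricted set departs from the all-randomised set. These points stand and shape the fix. Because serostatus is fixed before allocation, the comparison within seronegative women remains randomised.

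**Day-21 blood.** A reader might call this a contradiction. Swabs and blood share one row and its marks, the baseline sentence sits under Enrolment, and the visit text is silent on blood. It is an ambiguity that needs clarifying, no more.

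**Conclusion.** The point holds as a cheap improvement. The prevention population and event rest on one negative and one later positive PCR, although pre-randomisation serum is taken from every woman. Contacts infected before entry can be counted as uninfected, and a later positive swab in them may be counted as an incident infection.

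A reader might infer that this could produce a spurious benefit. It would not: such women are balanced between arms in expectation, so with equal q the effect is dilution towards RR 1 and loss of power. A reader might also infer that restriction recovers the planned 80%. It does not: it keeps power at 74–64% for s of 5–15%, unless more women are randomised.

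The loss avoided by restriction runs from nothing at q = 0 to 32 points at s = 15% and q = 10%. It rests on assumed s and q, on equal carry-over in both arms, on no new infections among seropositive women, and on an assay that classifies correctly.

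**What to change.** - **Analysis (5.i):** pre-specify the prevention comparison in contacts who are both PCR-negative and antibody-negative on the pre-randomisation sample. Report it alongside all randomised PCR-negative contacts (intention to treat).
- **Assay:** test the baseline sera in batches, blind to arm, with assay and cut-off fixed before unblinding. Enrolment need not wait for the result.
- **Fallback:** if the assay is not validated in time, keep the intention-to-treat set as the main analysis and the seronegative set as the pre-specified supporting analysis.
- **Day-21 blood:** reconcile the SARS-CoV-2 testing and follow-up visit text in 5.c with the shared row in Table 1. If blood is taken, use paired serology to support the classification of incident infections.

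**Cost.** Mainly wording, since the baseline samples and an assay are already planned. The seronegative set is smaller; keeping 257 per arm would mean randomising 271–303 at s of 5–15%. The assay may misclassify some women, and very early infections that are still seronegative will remain undetected.

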#### **b) Treatment arm allocation**

Participants will be then randomized in a 1:1 ratio to HCQ (400 mg/day for three days, followed by 200 mg/day for 11 days) or placebo (2 tablets for three days, followed by one tablet for 11 days).

Allocation of participants to study arms will be done centrally by the trial's Sponsor (the Barcelona Institute for Global Health, ISGlobal) by block randomization. This method will ensure balanced allocation to both arms. The electronic CRF will assign automatically a study number to each participant, depending on her study group and recruitment site. Each number will be related to a treatment number, which assigns them to one of the study arms. Randomizations lists with treatment assignment for each study participant will be concealed in opaque sealed envelopes and only open in case of urgent need following study unblinding procedures.

A study card will be given to the participant in order to facilitate their clinical management in case they attend primary care centres or other hospitals.

#### **Administration of study drugs**

Study tablets will be identically packaged in small opaque bottles. All study personnel, investigators and the participants will remain blinded throughout the trial.

Participants will receive a bottle containing 19 tablets of study medication. They will be instructed to take two tablets for first three days and one tablet for the following 11 days. The first day of treatment, drug administration will be supervised.

Women vomiting within the first 30 minutes of drug administration will be given a second full drug dose; women vomiting after 30-60 minutes of study tablets administration will be given an additional half dose of the drug.

#### **Follow-up and assessment of treatment adherence**

Participants will be contacted by phone daily during the intervention period by study personnel to assess general health condition, as well as the drugs' tolerability and potential adverse events. Treatment adherence and the intake of any concomitant medication will be also requested daily. Information regarding any unscheduled study visit to the hospital will be registered.

#### **Household and follow-up visits**

At day 21 after initiating study drugs' administration (one week after treatment completion), study personnel will visit women at home or at the hospital to collect a nasopharyngeal and oropharyngeal swabs for PCR -SARS-CoV-2 and to perform an ECG.

The study personnel will assess treatment adherence by requesting and counting if there are remaining study pills.

#### **End of pregnancy/ New-born assessments**

**a) Maternal clinical examination and assessments**

At the time of end of pregnancy (delivery or miscarriage) the outcome of the pregnancy will be recorded onto the study questionnaires.

**b) Placental sample collection**

In a sub-sample of study participants (n=120, randomly selected from the three study groups), a placental sample will be collected for histological examination. Within minutes of placental expulsion, the fetal surface of the placenta will be disinfected and incised with a sterile scalpel, and 2 swabs and biopsies (close to the umbilical cord and peripheral margin) will be obtained.

**c) New-born assessments**

A 5 ml blood sample for SARS-CoV-2 for Ig G and Ig M determination will be collected from the umbilical vein once the baby's umbilical cord has been cut and clamped. Information on the new-born anthropometrical parameters and clinical status will be recorded onto the study eCRF.

A nasopharyngeal aspirate will be collected 12 to 24 hours after birth for PCR- SARS-CoV-2 infection assessment.

**d) Miscarriage and other adverse pregnancy outcomes**

If the outcome of the pregnancy is a miscarriage or stillbirth, women will be visited at the study facilities and the same study procedures will be applied.

**Infant's check at one month of age**

The health status on the infant will be checked by a telematics clinical visit at one month of age.

**Unscheduled visits**

Study participants reporting sick at the phone or home visits will be recommended to contact the study hospitals by phone and follow their instructions. Every unscheduled visit of the woman from enrolment until delivery will be recorded onto the study eCRF.

**a) Physical and clinical examination**

Gestational age, blood pressure and axillary temperature will be registered. Suggestive symptoms of SARS-CoV-2 infection will be recorded

**b) Other medications**

Any concomitant treatment or history of treatment since the last visit will be recorded in the study eCRF. In addition, information on adverse events related to study drugs will be collected.

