#### Secondary endpoints

##### Maternal/Foetal

1. Incidence of COVID-19 disease during pregnancy
2. Incidence of COVID-19-related admissions
3. Incidence of all-cause admissions
4. Incidence of all-cause outpatient attendances
5. Mean duration of symptoms-signs of COVID-19

6. Frequency and severity of adverse events
7. Incidence of preeclampsia
8. Incidence of gestational diabetes
9. Incidence of SARS-CoV-2 infections during pregnancy
10. Prevalence of intrauterine growth restriction (<10th centile according to local standards) (21)
11. Maternal mortality rate

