### Adverse Events

#### *Definition of an Adverse Event (AE):*

Any untoward medical occurrence in a subject to whom a medicinal product has been administered, including occurrences which are not necessarily caused by or related to that product.

An AE can therefore be any unfavourable and unintended sign (including a clinically significant abnormal finding), symptom or disease temporally associated with the use of a medicinal product, whether or not considered related to the medicinal product.

All AEs should be treated appropriately. Treatment may include one or more of the following:

- no action taken (i.e. further observation only)
- study drug dosage adjusted/temporarily interrupted
- study drug permanently discontinued due to this adverse event
- concomitant medication given
- non-drug therapy given
- patient hospitalized/patient's hospitalization prolonged.

The action taken to treat the adverse event will be recorded on the AE form. Once an adverse event is detected, it will be followed until its resolution or until it is judged to be permanent, and assessment will be made at each visit (or more frequently, if necessary) of any changes in

severity, the suspected relationship to the study drug, the interventions required to treat it, and the outcome.

Information about common side effects already known about the study drug will be included in the patient informed consent and will be discussed with the patient during the study as needed.

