#### **Monitoring and reporting of Adverse Events**

Safety will be evaluated in the mother, the foetus and the newborn. Active safety monitoring will consist in daily phone visits to study participants from the initiation of treatment administration to assess drug tolerability and record all Adverse Events (AEs). In addition, a health facility-based passive surveillance system will be established to capture unscheduled visits of participants during follow-up.

The Principal Investigators (PI) at each study site will be responsible for recording, managing, and reporting of the AEs and SAEs as per study protocol. All AEs will be recorded in the AE form, and the DSMB will agree which SAEs and in what time frame will be reported.

All SAEs will be recorded on the SAE form and will be reported within 24 or 48 hours to the sponsor's (ISGlobal) Safety Coordinator, the CRO Dynamic Solutions, and to the DSMB as per study protocol. A flowchart will be provided to each study site to train the procedures for assessing AEs and reporting requirement according to severity and expectedness as well as persons responsible for recording and reporting of AEs/SAEs.

All participants enrolled in the trial will be educated at the beginning of the study on how to and whom to contact if they experience any untoward event and/or get admitted to the hospital.

In addition, Interim Safety Reports and Annual Safety Reports will be prepared by the Safety Coordinator and the CRO Dynamic Solutions and distributed to the local Ethic Committee, Sponsor, and DSMB as agreed in the study protocol.

The CRO Dynamic Solutions will ensure that AEs and SAEs are reported in compliance with International Conference on Harmonisation (ICH) Good Clinical Practice (GCP) guidelines and current international legislation during COVID-19 pandemic.

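### The unscheduled-visit procedure describes adverse-event collection as drug-related events, at odds with the protocol's all-event rule, so some non-serious events could go unrecorded

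*Protocol*

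**What the plan says.** Section 5.c, Unscheduled visits, sets out what happens when a participant is seen outside the schedule. The visits count over a long period: "Every unscheduled visit of the woman from enrolment until delivery will be recorded onto the study eCRF". Sub-item a) lists a short examination. Sub-item b), headed Other medications, asks for concomitant treatment and then adds: "In addition, information on adverse events related to study drugs will be collected". This is the only sentence in the unscheduled-visit procedure about collecting adverse events.

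The safety section (5.e) uses a wider scope. Its definition of an adverse event is explicit on cause: "including occurrences which are not necessarily caused by or related to that product". Its reporting rule is equally plain: "All AEs will be recorded in the AE form". It also makes unscheduled visits part of the safety system: "a health facility-based passive surveillance system will be established to capture unscheduled visits of participants during follow-up". The secondary maternal endpoint has no relatedness limit either: "Frequency and severity of adverse events".

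**The concern.** Read literally, the unscheduled-visit instruction makes a causality judgement the condition for collecting an event. Everywhere else that judgement is made about an event already on the form. Five hospitals and the builders of the eCRF have to turn this text into a working page, and they could resolve the conflict differently.

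An event that is never collected cannot be recovered at the analysis, whatever the analysis plan says. Safety is named among the main objectives in the synopsis and is secondary objective 3. The value of a randomized safety comparison lies largely in finding effects that nobody suspected, and a relatedness screen at the point of collection works against exactly those events.

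**Working it through.** The protocol states no figure on this point, so the check compares the texts.

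**1. The rules side by side**

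| Place in the protocol | Scope of events |
|---|---|
| 5.c Unscheduled visits, b) Other medications | Events related to study drugs |
| 5.e Definition of an Adverse Event | Any event, related or not |
| 5.e Severity, relationship and outcome | Relationship graded in five classes, the lowest being definitely unrelated |
| 5.e Serious Adverse Events | Relationship is a field on the AE/SAE form, with a not-suspected option |
| 5.e Monitoring and reporting | All AEs on the AE form, all SAEs on the SAE form |
| 5.a Secondary endpoints, item 6 | All adverse events |
| 5.i Safety population | Safety analysed by arm, no relatedness limit |

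The first row stands alone. If all events were meant there too, its qualifier has no function. If the qualifier is applied, the unrelated categories would hardly be used at these visits.

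**2. What else would catch a missed event**

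- *Treatment days 1 to 14:* "Participants will be contacted by phone daily during the intervention period by study personnel". The monitoring section says that these calls record all adverse events.
- *Day 21:* Table 1 marks adverse events at the household visit.
- *After day 21:* Table 1 marks adverse events under Pregnancy follow-up, with no relatedness limit. The text of 5.c, however, describes no scheduled maternal study visit between day 21 and the end of pregnancy. The items marked in that column largely match those listed for unscheduled visits, so the column may be the same contact. Table 1 has no adverse-event mark at delivery.
- *At any time:* serious adverse events are recorded regardless of cause. They include hospitalization, and the protocol also treats all grade 3-4 toxicities as serious.
- *Separate endpoints:* preeclampsia, gestational diabetes, growth restriction, all-cause admissions, all-cause outpatient attendances, maternal mortality, foetal loss, preterm birth and malformations do not depend on causality.

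**3. What is left**

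An event is at risk only if it is non-serious, surfaces only at an unscheduled visit, is judged unrelated, and is seen where the sentence is followed literally. Most of that exposure falls after day 21.

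**4. Size**

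Only a ceiling on exposure time can be given. Entry requires more than 12 weeks of gestation. Assuming entry just after week 12 and delivery at week 40, the window is 40 − 12 = 28 weeks, of which 28 − 3 = 25 weeks fall after day 21. Women who enter later have less, and the total is 714 women at most. The protocol gives no rate of unscheduled visits, no adverse-event rate and no share judged unrelated, so no number of lost events follows.

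**5. Direction**

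Suppose a fraction *f* of a given type of event is lost. Staff are blinded (5.c, Administration of study drugs), so take *f* as the same in both arms. With expected counts A and B, the recorded counts are (1 − *f*)A and (1 − *f*)B. The ratio A/B is unchanged, but fewer events are available to detect a difference. *f* would plausibly be larger for unexpected events than for the gastrointestinal and skin effects that the protocol lists as known, so sensitivity suffers most for the unexpected ones.

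**The case against.** The strongest reply is that this is one additive sentence under a sub-heading about medication. It contains no word such as *only*, and the dedicated safety section states the all-event rule without exception. A site that reads the whole protocol has a clear instruction. That stands as far as intent goes: the protocol chooses all-cause collection, and this is a local inconsistency of wording, not a design decision. It does not remove the need to edit the one sentence that governs these visits.

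Several stronger readings are tempting, and the document does not support them:

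- *The whole safety comparison is filtered by causality.* It is not. The daily calls record all events throughout treatment, and Table 1 also schedules adverse events at day 21 and at pregnancy follow-up.
- *Every unrelated event at an unscheduled visit is lost, including obstetric and cardiac events.* Serious events are recorded whatever their cause, and the main obstetric outcomes are endpoints in their own right.
- *Sites have nothing but the known side-effect profile to judge by.* Section 5.e gives five causality definitions, with a broad class for possible relationship, and plans a toxicity table and a site flowchart.
- *The arms are biased against each other.* Causality is judged blind, and nothing in the document shows different losses by arm.

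The adverse-event mark under Pregnancy follow-up cuts both ways. If the column is a separate contact, it may recover some events. If it covers unscheduled visits, Table 1 already contradicts the sentence. Either way the texts need to agree.

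**Conclusion.** The inconsistency is real and narrow. The unscheduled-visit sentence conflicts with the definition, the recording rule, the relationship field and the endpoint. If it is followed literally, non-serious adverse events that surface only at unscheduled visits and are judged unrelated could go unrecorded, mainly after day 21. Serious events, events from the daily calls and day 21, and the obstetric endpoints are untouched.

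The likely consequence is under-ascertainment and reduced sensitivity, of a size that the protocol does not allow anyone to estimate. Bias between arms is not demonstrated. The conclusion assumes that at least some sites or the eCRF page would apply the qualifier as written. If all of them apply the safety section's rule instead, nothing is lost. The change is still worth making, because the loss could not be repaired at analysis and the correction is nearly free.

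**What to change.** In section 5.c, Unscheduled visits, b), replace the phrase limiting collection to drug-related events with: *all adverse events, whether or not considered related to study drug*. Record the relationship afterwards on the AE form, using the classes and fields that section 5.e already provides. Align the eCRF page for unscheduled visits with that wording.

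The cost is a few words in the protocol, one eCRF page and slightly more adverse-event entries per unscheduled visit. Design, sample size and analysis do not change.
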